## Abstract

**Background:**

Intralipid is a necessary fatty acid carrier that has been safely used as an energy supplier in the clinic. It has played an important role in rescuing the cardiac arrest caused by local anesthetic toxicity. In recent years, experimental studies have shown that intralipid postconditioning (ILPC) could reduce myocardial ischemic/reperfusion (I/R) injuries. Our research group has innovatively conducted a pilot randomized controlled trial (RCT), and the results showed that ILPC could reduce the release of cTnT and CK-MB, biomarkers of myocardial I/R injury, in valve replacement surgery. However, the potential effects of ILPC on the clinical outcome of adult cardiac surgery patients are unclear. Intralipid postconditioning in patients of cardiac surgery undergoing cardiopulmonary bypass (iCPB) trial is aimed to further study whether ILPC could improve short-term and long-term clinical outcome, as well as cardiac function in adult cardiac surgery patients.

**Methods:**

The iCPB trial is an ongoing, single-center, prospective, double-blinded, large sample RCT. In total, 1000 adults undergoing cardiac surgery will be randomly allocated to either the ILPC group or the control group. The intervention group received an intravenous infusion of 2 mL/kg of 20% intralipid (medium-chain and long-chain fat emulsion injection C6~C24, Pharmaceutical) within 10 min before aortic cross-unclamping, and the control group received an equivalent volume of normal saline. The primary endpoints are complex morbidity of major complications during hospitalization and all-cause mortality within 30 days after surgery. The secondary endpoints include (1) all-cause mortality 6 months and 1 year postoperatively; (2) the quality of life within 1 year after surgery, using the QoR-15 questionnaire; (3) the postoperative cardiac function evaluated by LVEF, LVEDS, and LVEDD, and the myocardial injury evaluated by CK-MB, cTnT, and BNP; and (4) short-term clinical outcomes during hospitalization and total cost are also detailed evaluated.

**Discussion:**

The iCPB trial is the first to explore ILPC on the clinical outcome of adult cardiac surgery patients. The results are expected to provide potential evidences about whether ILPC could reduce the morbidity and mortality and improve the cardiac function and quality of life. Therefore, the results will provide a rationale for the evaluation of the potentially clinically relevant benefit of intralipid therapy.

**Trial registration:**

Chictr.org.cn ChiCTR1900024387. Prospectively registered on 9 July 2019.

## Background

Myocardial ischemia/reperfusion (I/R) injury [1] is an important factor affecting cardiac function and prognosis in patients of cardiac surgery. The underlying mechanisms include oxidative stress, inflammatory reaction, calcium overload, ion channel dysfunction and increased membrane permeability, energy metabolism disorders, etc. [1]. These mechanisms interrelated with each other, and most importantly, the energy metabolism disorders are the initial link. Improving myocardial energy metabolism can reduce myocardial I/R injury [2]. Since the myocardium relies mainly on fatty acid oxidation (FAO) instead of glycometabolism to provide energy, some experimental studies indicated that supplementing the exogenous FAO substrate can increase the supply of myocardial ATP and thus exert cardioprotection [3–7]. However, preischemic exposure of fatty acids will lead to insufficient FAO during the period of ischemia and cause cardiotoxicity injury subsequently. In the meanwhile, clinically, the myocardial ischemic processes are unpredictable, so the intervention of FAO during the period of reperfusion is more controllable and valuable.

Intralipid, a necessary fatty acid carrier, has been safely used as an energy supplier in the clinic for more than 50 years. It has also played an important role in rescuing the cardiac arrest caused by local anesthetic toxicity, which has been incorporated into several clinical guidelines [8–11]. In recent years, experimental studies have shown that lipid emulsion infusion just before reperfusion (i.e., intralipid postconditioning (ILPC)) could reduce myocardial infarct sizes, improve cardiac function, and reduce myocardial I/R injuries [12–16]. Subsequent mechanistic studies define that ILPC acts through the phosphorylation of glycogen synthase kinase-3β via PI3K/Akt/ERK pathways [12, 14, 15] and Caveolin2/STAT3/GSK-3β pathway [13] and ultimately inhibits the opening of mitochondrial permeability transition pore (mPTP), which is essential to mitochondrial calcium overload and reactive oxygen species (ROS). Meanwhile, Umar et al. [16] reported that the cardioprotective effects of lipid emulsion are mediated through G-protein-coupled receptor-40 (GPR40) in two animal models of I/R injury and bupivacaine-induced cardiotoxicity. On the other hand, it could simply be a metabolic switch from glucose to fatty acid metabolism that paradoxically protects the heart [7, 17]. Therefore, despite these interesting experimental findings, the potential clinical usage of intralipid in preventing myocardial I/R injury needs to be further investigated.

Based on the above background, our research group has innovatively conducted a pilot randomized controlled trial (RCT) to investigate whether ILPC would display the same cardioprotective effects in patients of cardiac surgeries, who were inevitably subject to I/R during cardiopulmonary bypass (CPB) [18, 19]. The results showed that ILPC could reduce the release of myocardial damage biomarkers of serum cardiac troponin T (cTnT) and creatine kinase-MB (CK-MB) after cardiac valve replacement surgery, and the total 72-h postoperative area under the curve (AUC) of cTnT and CK-MB were significantly reduced by 32.3% and 26.4% compared with control, respectively [19]. However, due to the relatively small sample content, there were no significant differences between the short-term clinical prognostic parameters such as LVEF, vasoactive inotropic drug score (VIS score), ICU time, length of hospital stays (LOS), morbidity, and mortality within 3 months after surgery.

Therefore, we design a large sample RCT to further study whether intralipid postconditioning could improve the short-term and long-term clinical prognosis as well as cardiac function of adult cardiac surgery patients undergoing cardiopulmonary bypass.

## Objective

Despite the numerous studies on the myocardial protective effects of different drugs and measures, there are only a handful of drugs and measures that can be safely and effectively applied to clinical practice [1, 20]. Our research is a large sample RCT conducted to assess whether intralipid postconditioning undergoing cardiopulmonary bypass surgery will reduce the all-cause mortality within 30 days after surgery and the rate of serious complications during hospitalization and improve the patient’s postoperative cardiac function. The outcome is expected to be the foundation for the future multicenter clinical trial to evaluate the potentially clinically relevant benefit of intralipid therapy. As has been safely and widely used in clinical practice, intralipid may play a novel and important role as a therapeutic intervention for ischemic heart diseases, if similar cardioprotective effects and better clinical outcomes are demonstrated clinically.

## Methods and design

### Study design

This iCPB study is a large sample, single-center, prospective, double-blinded, two-armed, randomized controlled trial with a 1:1 allocation ratio, testing the clinical outcome of intralipid postconditioning in adult cardiac surgery patients undergoing cardiopulmonary bypass. The protocol structure is written according to the Consolidated Standards of Reporting Trials (CONSORT) 2010 Statement guidelines and follows the Standard Protocol Items: Recommendations for Interventional Trials (SPIRIT) Statement. The SPIRIT checklist can be found in Additional file 1. The SPIRIT figure is illustrated in Fig. 1, and the flow chart in Fig. 2. The study will be conducted in West China Hospital of Sichuan University, China. More than 2500 open-heart procedures with CPB are performed there each year.

**Fig. 1 Fig1:**
[figure not shown]
Schedule of enrollment, interventions, and assessments according to Standard Protocol Items: Recommendations for Interventional Trials (SPIRIT)

**Fig. 2 Fig2:**
[figure not shown]
Flow chart

### Ethical approval and trial registration

This clinical study protocol has been approved by the Biomedical Research Ethics Committee of West China Hospital of Sichuan University on 4 July 2019 (approval number 2019(324)). The trial has been prospectively registered in the Chinese Clinical Trials Registry (ChiCTR) (www.chictr.org.cn) with the registration number ChiCTR1900024387 on 9 July 2019.

### Participants

We plan to enroll 1000 participants undergoing a cardiopulmonary bypass (CPB) for any elective cardiac surgical procedure via a median sternotomy such as procedures that involve the valves, coronary arteries, or aorta, or combined procedures. Written informed consent will be obtained from all patients before inclusion. The consent form and patient information materials are available from the corresponding author on request.

### Inclusion criteria

Patients will be eligible for enrollment if they meet all the following criteria:
Aged 18–70 years oldScheduled to undergo selective cardiac surgery with median sternotomy under CPBClassified by the American Society of Anesthesiologists (ASA) physical status classification scheme of classes I–IIISigned informed consent

### Exclusion criteria

Patients who meet any of the following criteria will be excluded from participation:
Redo cardiac surgeryExperienced cardiogenic shock or cardiac arrest, left ventricular ejection fraction (LVEF) less than 30%, positive baseline serum cTnT or CK-MBAortic arch and other deep hypothermic circulatory arrest surgery, such as pulmonary thromboendarterectomyHeart transplantationUncontrolled hypertension (systolic pressure ≥ 180 mmHg or diastolic pressure ≥ 110 mmHg)Hyperlipidemia (TC ≥ 6.2 mmol/L or LDL-C ≥ 4.1 mmol/L)Significant hepatic (international normalized ratio > 2.0), pulmonary (forced expiratory volume-1 < 40% predicted, PaO2/FiO2 < 120) or renal disease (serum creatine level > 150 μmol/L)Severe coagulation dysfunction (Plt, PT, APTT, TT, FIB, and D-dimer were abnormal at the same time.)Any disorder associated with immunological dysfunction (e.g., malignancy or positive serological test for the HIV) in the last 6 monthsCurrent infections (meet at least two of the four SIRS diagnostic criteria: body temperature > 38 °C or < 36 °C, HR > 90/min, R > 20/min or PCO2 < 32.33 mmHg, WBC > 12 × 10^9^/L or < 4 × 10^9^/L or immature WBC > 10%)Pregnant womenPreoperative treatment with intralipid in the last 1 monthPreoperative treatment with nicorandil (an adenosine triphosphate-sensitive potassium channel opener) or sulfonylurea (an adenosine triphosphate-sensitive potassium channel blocker)Participating in other interventional studies

### Randomization/blinding

Patients who meet the enrollment criteria will be randomized 1:1 to either control or ILPC group. Randomization will be performed with the use of a computer-generated randomization sequence from a random number table. The investigator who is responsible for grouping visits the patients the day before surgery and gets the informed consent. Once the patient is qualified, he determines the serial number and the random number of the patient and writes on the case report form (CRF). Any intraoperative event or deviation from the protocol is recorded on the CRF. Allocation concealment was maintained until the time of CPB initiation by using opaque, numbered, and sealed envelopes. Other researchers, such as data collectors and data analysts, will be unaware of the patient grouping. The perfusionists will be aware of patients’ group allocation because they will provide the trial intervention, but they will not be involved in either the postoperative treatment or the analysis. Due to the color difference between intralipid and saline, the intravenous infusion of the two fluids will be shielded.

The patients, surgeons, ICU physicians, data collectors, and data analysts are not aware of the trial grouping in the whole process; if patients are seriously ill, then unblinding will need to be undertaken. Any intraoperative event or deviation from the protocol is recorded on the CRF.

### Interventions

Patients who meet the enrollment criteria will be randomized 1:1 to either the control or the intralipid postconditioning (ILPC) group.

Patients in the ILPC group will receive an intravenous infusion of 2 mL/kg of 20% intralipid (medium-chain and long-chain fat emulsion injection C6~C24, Pharmaceutical) less than 10 min before aortic cross-unclamping. Intralipid should be infused over 10 min in constant speed, and standard or usual care will be given to patients before and after the intervention. The dose of intralipid is chosen on the basis of the bolus dose when it is used in rescuing the cardiac arrest caused by local anesthetic toxicity [8–11]. Patients in the control group received an equivalent volume of normal saline 10 min before aortic cross-unclamping. There will be no special criteria for discontinuing or modifying allocated interventions.

Three investigators ([name], [name], and [name]) will explain the treatment intervention in detail and supervise the compliance of intervention throughout the entire procedure (from maintenance of anesthesia to transport to ICU).

### Study endpoints

The primary endpoints are complex morbidity of major complications during hospitalization (all systemic organ complications are graded as I–V in Table 1) and all-cause mortality within 30 days after surgery. Each individual outcome of the composite endpoint will be analyzed separately.

**Table 1 Tab1:** Grade of complication outcome of the subjects

Grade of complication outcome of the subjects	
I	Healed after temporary treatment
II	Lead to longer hospital stay
III	Life-threatening, but can be basically recovered during hospitalization
IV	Resulting in injuries for 30 days or longer after surgery, the quality of life is significantly reduced
V	Death within 30 days after the surgery (during the study period)

Note: The end of the operation until 24:00 on the day is 0 days after surgery, and the next day after surgery is 00:01–24:00 and so on

The secondary endpoints include (1) all-cause mortality 6 months and 1 year postoperatively; (2) the quality of life within 1 year after surgery, using the 15-item Quality of Recovery Questionnaire (QoR-15) [21, 22]; (3) the postoperative cardiac function evaluated by LVEF, LVEDS, and LVEDD at time points of 1 week, 1 month, 6 months, and 1 year postoperatively, and the myocardial injury evaluated by CK-MB, cTnT, and BNP at time points of 2 h and 24 h postoperatively; and (4) short-term clinical outcomes during hospitalization (postoperative awakening time, mechanical ventilation time, ICU time, length of hospital stay) and total cost are also detailed evaluated.

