## Statistical considerations

### Sample size estimate

PASS 15.0 software (NCSS Corp., Kaysville, UT, USA) is used to calculate the sample size. The sample selected for this trial was based on the results of a meta-analysis published by our research team, exploring the influences of inhalation anesthesia compared with total intravenous anesthesia on the patients’ outcomes after valve surgery [23]. The study included 13 randomized controlled trials (a total of 962 patients undergoing heart valve surgery) and found that the 30-day mortality rate was 5.3% and complex morbidity of major postoperative complications was 27%. Taking the complex morbidity of major complications in the meta-analysis as a control, the study has 80% power to detect a 30 relative risk reduction for the primary outcome of complex morbidity at a significance level (alpha) of 0.05 (two-sided), with an allowance of 10% of patients lost to follow-up or withdrawn from the study; finally, the calculated sample size of this study is about 1000 cases (500 cases each group).

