### Data analysis

SPSS 22.0 software (IBM Co., Armonk, NY, USA) will be used to analyze the data. Baseline characteristics will be compared using chi-squared or Fisher’s exact tests. The continuous variables that have a normal distribution will be presented as the mean ± standard deviation (SD) or numbers (percentages) and compared using the *t* test or nonparametric test. The incidence of primary and secondary endpoints was measured using the chi-squared test or Fisher’s exact tests. A sensitivity analysis using the modified intention to treat (mITT) approach will also be performed. As a composite outcome, each individual outcome should be analyzed individually. Subgroup classification will be performed according to different types of surgery, Cox analysis will be used to analyze the mortality of different types of surgery, and multivariate logistic regression analysis will be used to correct for risk factors. Variables tested in the model will be selected if *P* < 0.10 or if they are clinically relevant. Results are considered statistically significant if *P* < 0.05. Two-sided significance tests will be used throughout.

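### The primary outcome is defined inconsistently, so the 5% error rate is not secured, and 30-day mortality is named primary without being powered

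*Protocol article*

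**What the plan says.** The article describes the primary outcome in three ways.

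- **Two endpoints.** The Abstract (Methods) states: "The primary endpoints are complex morbidity of major complications during hospitalization and all-cause mortality within 30 days after surgery". The Study endpoints section repeats the plural.
- **One composite.** The next sentence under Study endpoints reads "Each individual outcome of the composite endpoint will be analyzed separately". Data analysis agrees: "As a composite outcome, each individual outcome should be analyzed individually".
- **Morbidity alone.** Under Sample size estimate, "the study has 80% power to detect a 30 relative risk reduction for the primary outcome of complex morbidity" (the percent sign is missing; I read 30%). A 30-day mortality rate of 5.3% is given beside the 27% morbidity rate but is not used.

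Table 1 makes death within 30 days Grade V of the complication scale, so the second named endpoint also lies inside the first. Data analysis sets one threshold, P<0.05, for all results. The article gives no division of alpha, no testing order, and no statement of whether one or both endpoints must succeed.

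**The concern.** These descriptions imply different trials. With two separate primaries, either of which can carry a positive conclusion, two tests at 0.05 exceed the planned error rate. If both must succeed, the error rate is protected but power falls to that of the weaker endpoint, roughly. With one composite, or morbidity alone, a single test at 0.05 is sound.

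The Objective section lists both lower 30-day mortality and fewer serious complications as aims, so it does not settle the matter. Two misreadings of the result are therefore open. A null mortality result could be reported as a failed primary in a trial that had little chance of detecting the effect. An isolated P<0.05 on mortality could be reported as a primary success.

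**Working it through.** **Inputs.** From Sample size estimate: control rates 27% (complex morbidity) and 5.3% (30-day mortality), 30% relative reduction for morbidity, two-sided alpha 0.05, power 80%, 10% loss, 500 per group. After 10% loss, 500 × 0.9 = 450 evaluable per arm. From Data analysis: chi-squared or Fisher's exact test.

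**Formulas.** With d = p1 − p2, p̄ = (p1 + p2)/2, s0 = √[2p̄(1−p̄)] and s1 = √[p1(1−p1) + p2(1−p2)]:

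- n per arm = (1.96·s0 + 0.842·s1)² / d²
- power = Φ[(d√n − 1.96·s0)/s1]

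**Step 1: the plan's own figure (morbidity).** p1 = 0.27, p2 = 0.27 × 0.7 = 0.189, d = 0.081, s0 = 0.5947, s1 = 0.5919.

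- Without continuity correction: n = 422 per arm; 422/0.9 = 469; 938 in total.
- With continuity correction: n = 447 per arm; 447/0.9 = 497; 994 in total. This reproduces the stated 1000.
- Power at 450 per arm: Φ(0.934) = 82.5%. At 500 per arm: 86.2%.

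**Step 2: mortality as a primary.** The protocol states no mortality effect, so the same 30% reduction is assumed: p1 = 0.053, p2 = 0.0371, d = 0.0159, s0 = 0.2933, s1 = 0.2931.

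- Power at 450 per arm: Φ(−0.811) = 20.9%. At 500 per arm: 22.7%.
- n for 80% power: 2,671 per arm; 2,968 after 10% loss; 5,936 in total.

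Power for other assumed reductions in mortality:

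| Relative reduction | 450 per arm | 500 per arm |
|---|---|---|
| 20% | 11.2% | 12.0% |
| 30% | 20.9% | 22.7% |
| 40% | 35.1% | 38.3% |
| 50% | 53.0% | 57.3% |
| 60% | 71.4% | 75.9% |

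At 450 per arm, 80% power needs a reduction of about 65%.

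**Step 3: error rate under each reading.**

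- *Either primary suffices, independent tests:* 1 − 0.95² = 9.75%.
- *Either suffices, every death also counted as morbidity:* the correlation is (0.053 − 0.27 × 0.053)/√(0.27 × 0.73 × 0.053 × 0.947) = 0.389. The bivariate normal probability that at least one |Z| exceeds 1.96 is 9.3%.
- *One composite, morbidity alone, or both must succeed:* at most 5%.

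**Step 4: power if both must succeed.** With the same correlation and 450 per arm, the probability that both tests are significant is about 20%.

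**Step 5: power for one composite.** The control rate is assumed to lie between 27% (every death already counted in morbidity) and 27% + 5.3% = 32.3% (no overlap), with the same 30% reduction. At 450 per arm, power is 82.5% at 27% and 90.4% at 32.3%.

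**The case against.** The best defence is that the article means a single composite, loosely written in the plural. The word composite follows directly after the two elements are named, it recurs under Data analysis, and Table 1 already places death on the complication scale. On that reading the error rate is 5% and power is about 82% or more. This is plausible and informs the fix. It is not certain: the Abstract and Study endpoints both say endpoints in the plural, and Sample size estimate gives the two rates separately and powers only one.

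Reporting the components of a composite is ordinary practice, and nothing says that a component result alone makes the trial positive. That stands; the component analyses are not the fault.

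A success rule may also sit in a full protocol or analysis plan that is not shown. So the missing rule is not the finding in itself. The conflicting naming of the primary outcome within this article is, and an unseen document does not remove it.

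Two stronger readings are tempting. A reader might infer that the stated 80% power is false. It is not: it is claimed for complex morbidity only and reproduces there. A reader might also infer that the 5% error rate definitely fails. The documents do not support that, because it is exceeded only if either endpoint alone can make the trial positive.

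**Conclusion.** The point holds in a conditional form: the primary outcome must be reconciled to one definition, because the article as written does not secure the 5% error rate. The size of the problem depends on the reading: about 9.3% to 9.75% if either primary suffices, and no inflation under the other three.

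The sample size is adequate for complex morbidity. The power fault is that mortality is also called primary with no power behind it. The 21% to 23% figure rests on the protocol's 5.3% control rate and on an assumed 30% reduction. Over assumed reductions of 20% to 60%, power runs from 11% to 76% and never reaches 80%.

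**What to change.** Reconcile the Abstract, Study endpoints, Sample size estimate and Data analysis as follows.

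1. Define one yes/no primary outcome per patient, tested once at two-sided 0.05. The composite of major complication or death from any cause within 30 days is preferable, because it fits the wording of Data analysis and Table 1. Use the definition of major complication that underlies the 27% rate. Table 1 alone does not supply one, since its scale starts at complications that heal with temporary treatment.
2. Make 30-day mortality and the other components secondary, reported as estimates with 95% confidence intervals and no separate claim of success.
3. State under Sample size estimate that the 80% power applies to the single primary only and that mortality is not powered. Give the mortality power together with its assumed effect, for example about 21% at 450 per arm for a 30% reduction.

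The cost is wording. No more patients are needed if the composite control rate lies in the assumed 27% to 32.3% range. The downside is that a mortality-only result can no longer be claimed as a primary success. Naming morbidity alone as the primary would also hold the error rate at 5%, but it fits the composite wording less well.

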### Data collection

All the related data are collected on the CRF. Preoperative data include general information about age, height, weight, and current and past medical history, especially heart disease history. The classification of the American Society of Anesthesiologists (ASA) was used to assess the risk within 24 h before surgery. Intraoperative data include the type and duration of surgery procedure, duration of CPB and aortic cross-clamp, method of anesthesia, and duration of anesthesia. Postoperative data include the morbidity and mortality; cardiac function evaluated by LVEF, LVEDS, and LVEDD; myocardial injury evaluated by CK-MB, cTnT, and BNP; short-term clinical outcomes during hospital stay (postoperative awakening time, mechanical ventilation time, ICU time, length of hospital stay); and total cost. The follow-up data include quality of life at three time points (1 month, 6 months, and 1 year), using the 15-item Quality of Recovery Questionnaire (QoR-15) and the echocardiography to evaluate the cardiac function.

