Our research group has conducted a pilot study and showed promising results that ILPC induced a significant reduction of postoperative cTnT and CK-MB release in patients undergoing cardiac valve replacement surgery [18, 19]. Moreover, a single intravenous bolus of intralipid (2 mL/kg, 20% intralipid) did not bring abnormal lipid metabolism and was found to be safe, with no perioperative hepatic or renal dysfunction or any other significantly related complications [18, 19]. However, the sample size of the pilot study is small, and it is uncertain to know its influence on patient outcome. Here, we continue to conduct a large sample RCT to further study whether it could improve the cardiac function, the short-term and long-term clinical prognosis of adult cardiac surgery patients, not limited to valve replacement surgery. To our knowledge, this is the first clinical trial investigating the effects of intralipid postconditioning on patient outcome, including mortality, morbidity, and long-term life quality. Our data will provide a rationale for the evaluation of the potentially clinically relevant benefit of intralipid therapy.

Our research has certain limitations. First of all, due to intralipid being white emulsion, it was difficult to achieve the blinding of anesthetists and perfusionists. So even they will provide the trial intervention, but they will not be involved in either the postoperative treatment or the analysis. Secondly, since the inhaled anesthetic sevoflurane is considered to be significantly cardioprotective and the high-dose propofol has also been reported to have a certain myocardial protective effect [27–29], both of which are currently widely used in clinical anesthetics, how to reduce their interference on the results of intralipid postconditioning is of great importance. In our previous pilot study [18, 19], all included patients were given total intravenous anesthesia to eliminate the interference of sevoflurane. However, this does not rule out the role of propofol and is also not consistent with clinical practice. Therefore, in this large sample RCT, we do not limit the anesthesia methods, but will make strict statistics on the dosage of various anesthetics in the intervention group and the control group, so as to ensure the baseline data be comparable. Thus, the confounding factors and interference of the anesthetics will be effectively avoided, and at the same time, it was more consistent with the clinical routine.

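### The biomarker endpoints (cTnT, CK-MB, BNP) are compared by unadjusted two-group tests across mixed procedures; a log-scale model with planned surgery type would be more precise at almost no cost

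*Protocol article*

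**What the plan says.** Study endpoints, in the protocol article, lists as part of the third secondary endpoint "the myocardial injury evaluated by CK-MB, cTnT, and BNP at time points of 2 h and 24 h postoperatively".

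Data analysis says that continuous variables are summarised "and compared using the *t* test or nonparametric test". It ties the t test to normally distributed variables, so the nonparametric test is the natural choice for a skewed marker. It names no transformation, covariate or effect measure for continuous outcomes. The adjusted models it names are Cox regression for mortality and logistic regression to correct for risk factors. Neither takes a continuous marker as its outcome. Surgery type is used to form subgroups.

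Participants admits valve, coronary, aortic and combined procedures. The Discussion confirms that the population is "not limited to valve replacement surgery", unlike the pilot. Surgery type is on the case report form: "Intraoperative data include the type and duration of surgery procedure".

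**The concern.** Injury markers are commonly right-skewed, and their level may well differ between, say, a single valve and a combined procedure. The planned procedure is known before allocation, so adjusting for it is legitimate. An unadjusted test instead counts differences between procedures as noise. If the markers are skewed and the rank test is used, the result is a p-value. The reader would not learn how large the reduction is or how uncertain it is.

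These markers are the trial's most direct measure of the reperfusion injury that the treatment is meant to reduce. What is at stake is the precision and readability of that secondary result. Bias is not at issue, and neither is the primary endpoint.

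**Working it through.** **The plan's own figure.** The only sample size concerns morbidity: "the study has 80% power to detect a 30 relative risk reduction for the primary outcome of complex morbidity", from a control rate given as "complex morbidity of major postoperative complications was 27" per cent. The rates are 0.27 and 0.27 × 0.70 = 0.189. At two-sided alpha 0.05 the pooled formula gives 422 per arm. The continuity correction gives (422/4) × (1 + √(1 + 4/(422 × 0.081)))² = 447. Allowing 10% loss, 447/0.9 = 497 per arm, or 994 in total, which agrees with about 1000. No power is stated for the biomarkers.

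**Inputs for the biomarker check**
- Analysable patients: 500 × 0.9 = 450 per arm (from the document).
- Log-normal marker, total log-SD 1.0, with 0.8 as an alternative (assumed).
- Surgery type explains R² = 0.10, 0.25 or 0.40 of log variance (assumed).
- True reduction 15% (assumed), and 26.4%, the smaller of the two pilot figures.

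**Formulas**
- Log effect: d = −ln(1 − reduction). For 15%, d = 0.1625. For 26.4%, d = 0.3065.
- Standard error without adjustment: SD × √(2/450) = 0.0667 at SD 1.0.
- Standard error with adjustment: that value × √(1 − R²) = 0.0632, 0.0577 or 0.0516.
- Power = Φ(d/SE − 1.96). For the rank test, d/SE is multiplied by √(3/π) = 0.977.
- Raw-scale t test: CV = √(exp(SD²) − 1) = 1.31 and SE = CV × √((1 + (1 − reduction)²)/450).

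**Power for a 15% reduction**

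| Analysis | log-SD 1.0 | log-SD 0.8 |
|---|---|---|
| Raw t test | 46% | 73% |
| Rank test | 66% | 85% |
| Log scale, no covariate | 68% | 86% |
| Log scale + surgery type, R² 0.10 / 0.25 / 0.40 | 73 / 80 / 88% | 89 / 94 / 98% |

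Simulations with four surgery types agree within simulation error. At log-SD 1.0 they give 64% to 67% for the rank test and about 73% to 90% for the adjusted model. Most of the gain over the rank test comes from surgery type. The log scale alone adds about 2 points, but it supplies the estimate. Adjustment narrows the confidence interval by 1 − √(1 − R²), which is 5%, 13% or 23%.

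**Power for a 26.4% reduction, log-SD 1.0.** Raw t test: SE = 1.31 × √((1 + 0.736²)/450) = 0.0767, and Φ(0.264/0.0767 − 1.96) = 93%. Rank test: Φ(0.977 × 0.3065/0.0667 − 1.96) = 99%. The adjusted log model exceeds 99%. With a wider spread (CV 1.5, log-SD 1.09) the raw t test falls to 85%, and an unadjusted log-scale test has 99%.

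**The case against.** The strongest reply is that transformation, covariates and effect measure for a secondary biomarker belong in an analysis plan that is not shown, and that nothing stated is wrong. The comparison is unbiased, and subgroups by surgery type are planned. Much of this stands: there is no error or contradiction here. But the section does name the test for continuous variables, and a better one can replace it using data already collected. Subgroups divide the sample and do not remove procedure variance from the overall comparison.

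A second reply is that the gain depends on assumptions. That also stands. At R² = 0.10 the gain over the rank test is only 66% to 73% at log-SD 1.0, or 85% to 89% at 0.8. The raw t-test figures are not a fair picture of the plan if the markers are skewed, because the plan then points to the rank test.

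Three stronger readings are tempting, but the document does not support them.
- *A pilot-sized effect could easily be missed.* The 26.4% calculation shows otherwise.
- *The unadjusted tests are what prevents comparison with the pilot*, where "cTnT and CK-MB were significantly reduced by 32.3% and 26.4% compared with control". Those are reductions in a 72-hour area under the curve after valve replacement only. Samples at 2 h and 24 h cannot give that quantity under any model. Group means would in any case still give a crude percentage.
- *Preoperative BNP is not measured.* The schedule of assessments (Fig. 1) is not shown. The preoperative list in Data collection also omits cTnT, CK-MB and LVEF, which the exclusion criteria require before surgery. Absence of BNP from that list therefore proves nothing.

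**Conclusion.** The point holds as a minor, nearly free improvement in precision and reporting for one part of a secondary endpoint. Under the assumed 15% reduction and log-SD 1.0, moving from the rank test to the adjusted log-scale model raises power from about 66% to between 73% and 90%, depending on how much variance surgery type explains. At log-SD 0.8 the rise is from about 85% to between 89% and 98%. The log-SD, the variance share and the 15% effect are all assumptions, since the document gives none of them. The stated tests are valid, and the conclusion does not touch the primary endpoint or the sample size.

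**What to change.** In Data analysis, state that log cTnT, log CK-MB and log BNP at each time point will be analysed with a linear model containing arm and planned surgery type (valve, coronary, aortic, combined), and that the result will be reported as the ratio of geometric means with its 95% CI.

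Use the procedure planned before allocation. Keep cross-clamp, bypass and surgery durations out of the model, because they are completed after allocation and could be affected by it. If the assessment schedule already includes a preoperative BNP, add its log as a covariate in the BNP model.

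The cost is a change of wording. No extra patients, visits or assays are needed. If the case report form holds only the procedure performed, the planned one has to be taken from the preoperative record. The change should be fixed before unblinding.
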